### Design

The study uses a pragmatic design. It is a phase II, open-label, active control, single-centre, exploratory trial of the effectiveness, feasibility and acceptability of ENDs and liquid nicotine plus quitline counselling among AOD clients discharged from care compared to current best practice (combination NRT and quitline counselling) for smoking cessation and relapse prevention. Follow-up measures will be assessed at 6 and 12 weeks after discharge from the service. Due to the nature of the intervention, neither participants nor staff can be blinded to allocation. However, the data safety monitoring committee and the statistician responsible for the data analysis will be blinded. This trial is registered with the Australian New Zealand Clinical Trials Registry (ACTRN12617001205325p). This study has received ethics approval from the Eastern Health human research ethics committee (E16–2016) and the University of Newcastle human research ethics committee (H-2017-0249). The trial follows the recommendations for interventional trials guidelines (SPIRIT; see Additional file 1). The study schedule of enrolment, product supply and assessments is presented in Fig. 1.

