**Fig. 2 Fig2:**
[figure not shown]
Flow chart of participant recruitment and follow-up. AOD alcohol or other drugs, END electronic nicotine device, NRT nicotine replacement therapy, RA research assistant, Wk week

All potential participants will receive a copy of the participant information and consent form and the project RA will give a full verbal explanation of the trial (aims, procedures, risks and benefits) in lay terms. Potential participants will have the opportunity to discuss the trial and ask questions. Participants will be advised they can withdraw from the study at any time without prejudice and that their decision to participate in the trial or not will in no way affect the care they receive at the residential withdrawal unit. Following this process, the participant will be asked to provide written consent to participate in the study and complete the baseline survey. Consent will also be collected for the research team to use participant contact details at the end of the trial to possibly invite the participant to take part in a one-off telephone interview about their study experience.

After formal enrolment into the trial, participants will be assigned a unique study ID number, which will be in a re-identifiable format. The ID number will be used by the secure online survey platform, into which participants will enter their identifying information (follow-up contact details) and then proceed on to the baseline questionnaire items. The participant-identifying details will be stored separate to other data, while the ID number will be attached to both. Collection of the baseline data will be completed by the participant online via an iPad. At the end of the baseline survey, participants will be randomised 1:1 to an intervention via a computer-sequenced 4–6 block randomisation embedded in the iPad.

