### Outcomes

#### Primary outcome

The primary outcome is the continuous abstinence from smoking (defined using a modified version of the Russell standard [33]), that is, no more than five (tobacco) cigarettes after their discharge from the residential AOD withdrawal service. Sustained abstinence from discharge will be checked at each follow-up time point, i.e. by self-report at weeks 6 and 12. Sustained abstinence will be assessed from the date of the previous interview: “Since [date] did you smoke at all, even part of a cigarette?” and among those who did: “In the past 6 weeks (that is, since [date]), have you smoked a tobacco cigarette, even a puff?” with the response options: (1) no, not a puff, (2) 1–5 cigarettes or (3) more than five cigarettes.

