#### Secondary outcomes

Secondary outcome measures assessed at 6 and 12 weeks, include:i.7-day point prevalence smoking abstinence, based on: “Have you smoked at least part of a cigarette in the last 7 days?”ii.Point prevalence abstinence from all nicotine (including NRT and ENDs), defined as having not used any products containing nicotine in the previous 7 days at assessment.iii.Continuous abstinence post discharge from all nicotine (including NRT and ENDs).iv.Reported number of cigarettes smoked per day among those who relapse (a relapse is defined as 7 days of continuous smoking for previously daily smokers).v.Cravings, assessed by one item based on Taggar et al. [34]: “Currently, how often do you get strong cravings to smoke tobacco?” with the response options: (1) hourly or more often, (2) several times per day, (3) at least once a day or (4) less than daily.vi.Withdrawal, as assessed by the Minnesota Nicotine Withdrawal Scale [35, 36], an eight-item scale rating withdrawal symptoms on an ordinal scale ranging from 0 (not present) to 4 (severe).vii.Time to relapse, which will be determined for those who do relapse by asking when they first smoked after a quit attempt.viii.Feasibility, which will be assessed by collecting the recruitment rate, consent rate and attrition rate.ix.Acceptability, by asking about the extent of use of the nicotine products provided. This will be determined by a five-point Likert scale administered in the 6- and 12-week surveys. The following question will be asked: “Thinking about your use of and experience with the [product], please indicate your agreement with the following statements: it was effective at reducing my cravings; it was easy to use; it was enjoyable to use.” The response options are: (1) strongly disagree, (2) disagree, (3) undecided, (4) agree or (5) strongly agree. Those in the NRT group will be asked about each type of product individually.x.Number of subsequent quit attempts among those who relapsed.xi.Any adverse events reported during the study.xii.Treatment adherence (use of NRT, ENDs and quitline). Adherence to treatment will be measured by questions about product use in the 6- and 12-week surveys. Participants will be asked if they have used the products and if they are currently using the products. If they are not using the products, then they will be asked why, otherwise they all be asked about the frequency of use and if they use a combination of products.xiii.Process measures. The 6- and 12-week surveys will assess the use of any additional pharmacotherapies, general practice visits and the use of printed and online materials to aid in quitting. Records from the quitline database regarding number, length, content and timing of calls will also be collected. In addition, cost data will be recorded.

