### Statistical methods

#### Sample size estimation

We expect to recruit 100 clients over a 10-month period. Approximately 80% of clients to the service are smokers. We will be assuming 50% eligibility and consent into the trial, and 40% attrition at 12 weeks based on our current AOD research. A total of 60 participants at the 12-week follow-up will provide 30 smokers per experimental group. This trial has been designed to provide essential preliminary information for the development of an adequately powered larger superiority trial, including smoking prevalence, response and attrition rates.

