#### Statistical analysis plan

Data will be collected on recruitment and retention rates, which will aid the design of future larger trials. Primary cessation outcome analyses will be carried out on an intention-to-treat basis. We will use chi-squared tests to compute relative risks, 95% confidence intervals and two-sided *p* values for all binary variables, followed by adjusted multiple logistic regression analyses. Continuous outcomes (with 95% confidence intervals) will be analysed using generalised linear mixed methods regression for the main aims, with adjustments for covariates where necessary.

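### Time to relapse dates a different event from the one that defines relapse, does not start clearly at discharge, and as worded gives a time only to those who relapse

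*Protocol article*

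**What the plan says.** In the protocol article, three items under Secondary outcomes depend on relapse.

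- Item iv defines it: "a relapse is defined as 7 days of continuous smoking for previously daily smokers".
- Item vii dates it: "Time to relapse, which will be determined for those who do relapse by asking when they first smoked after a quit attempt".
- Item x counts further quit attempts among those who relapsed.

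The Primary outcome section uses another threshold and an explicit origin. Abstinence there means "no more than five (tobacco) cigarettes after their discharge from the residential AOD withdrawal service".

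The Inclusion criteria require only that a person smoked tobacco on entry, daily or not.

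The Statistical analysis plan section gives chi-squared tests and logistic regression for binary variables. For the rest it says: "Continuous outcomes (with 95% confidence intervals) will be analysed using generalised linear mixed methods regression for the main aims". It names no time-to-event method and no censoring rule. On follow-up, the Design section says: "Follow-up measures will be assessed at 6 and 12 weeks after discharge from the service".

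**The concern.** Four things do not fit together.

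1. **Event.** A week-long run of smoking makes someone a relapser, but the recorded date is that of the first smoking, which may come much earlier.
2. **Origin.** Item vii counts from a quit attempt, while the primary outcome counts from discharge. Item x expects repeated quit attempts, so the phrase does not identify one starting point.
3. **Coverage.** Relapse has no definition for an eligible person who did not smoke daily.
4. **Population.** On the plain wording a time exists only for relapsers. Treatment is meant to change who relapses, so a comparison within that group is not protected by randomisation.

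Time to relapse is among the secondary outcomes named in the abstract, and the Design section gives relapse prevention as a purpose. The trial is also meant to supply preliminary figures for a larger superiority trial. A distorted relapse estimate would carry over into that design.

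**Working it through.** **1. The plan's own figure.** The Sample size estimation section says "We expect to recruit 100 clients over a 10-month period" and assumes "40% attrition at 12 weeks based on our current AOD research". Then 100 × (1 − 0.40) = 60, or 30 per group, as stated. No figure in that section depends on time to relapse.

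**2. The definitions side by side.**

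| | Event | Start | Who has a value |
|---|---|---|---|
| Primary outcome | more than five cigarettes | discharge | all |
| Item iv | seven-day run of smoking | not given | those who smoked daily before |
| Item vii | first smoking | a quit attempt | those who relapse |

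Take a person who lapses once in week 1 and starts a seven-day run in week 10. Item iv makes them a relapser because of week 10, and item vii scores them at week 1, a gap of 10 − 1 = 9 weeks. A person who lapses and never smokes for seven days running gets no time at all.

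**3. A relapsers-only comparison under constant hazard.** The inputs are:

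- horizon T = 12 weeks (Design);
- NRT abstinence p0 of 9% to 33%, the range the Background gives for three trials of NRT with behavioural support, with 20% as a middle value;
- an assumed hazard ratio of 0.5, which doubles the median, as the Background reports for ENDs against patches.

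The illustration has no dropout and one clean event. The formulas are:

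- NRT hazard λ0 = −ln(p0)/T; END hazard λ1 = 0.5 × λ0; END abstinence p1 = exp(−λ1·T);
- median in everyone = ln 2/λ;
- median in relapsers by week 12 = −ln(1 − 0.5·F)/λ, where F = 1 − exp(−λT);
- restricted mean in everyone = F/λ;
- mean in relapsers = 1/λ − T·(1 − F)/F.

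For p0 = 9%: λ0 = 2.408/12 = 0.2007 and λ1 = 0.1003. The medians in everyone are 3.45 and 6.91 weeks. In relapsers they are −ln(0.545)/0.2007 = 3.02 and −ln(0.650)/0.1003 = 4.29.

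| p0 | p1 | Medians, all (ratio) | Medians, relapsers (ratio) | Restricted mean difference, all | Mean difference, relapsers | Share kept |
|---|---|---|---|---|---|---|
| 9% | 30.0% | 3.45, 6.91 (2.00) | 3.02, 4.29 (1.42) | 2.44 | 1.03 | 42% |
| 20% | 44.7% | 5.17, 10.34 (2.00) | 3.81, 4.82 (1.27) | 2.28 | 0.75 | 33% |
| 33% | 57.4% | 7.50, 15.01 (2.00) | 4.42, 5.18 (1.17) | 1.96 | 0.54 | 27% |

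Times are in weeks, and shares come from unrounded values. At a hazard ratio of 0.7 the shares kept are 47%, 36% and 29%.

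**4. The same comparison under a delay pattern.** The New Zealand trial cited in the Background had 6-month abstinence of 7.3% on ENDs and 5.8% on patches, with a doubled median time to relapse. I assume that the doubling applies among relapsers and that their times are exponential, truncated at the horizon. With relapser medians of 1 and 2 weeks over 26 weeks:

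- relapser means are 1.44 and 2.88, a difference of 1.44;
- the difference in everyone is (0.073 × 26 + 0.927 × 2.88) − (0.058 × 26 + 0.942 × 1.44) = 4.568 − 2.864 = 1.70;
- the share kept is 1.44/1.70 = 85%.

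NRT relapser medians of 1 to 3 weeks over 26 weeks give 85% to 98%. Medians of 1 to 2.5 weeks over 12 weeks, with the same abstinence figures, give 95% to 101%.

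**5. Direction.** Suppose four NRT participants relapse at weeks 1, 2, 10 and 12, a mean of 25/4 = 6.25. If ENDs prevent the last two, the END relapsers' mean is 3/2 = 1.5, and the better arm looks worse. The distortion can therefore even reverse the sign.

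**The case against.** Item vii can be read as data collection only. A relapse date can be asked only of someone who relapsed, and the sentence does not exclude censoring the others. The article is condensed, and a censoring rule and survival method for one secondary outcome may stand in an analysis plan that is not shown. The analysis section does not say that time to relapse counts as a continuous outcome or a main aim. This stands: a reader might infer that the plan prescribes a test of mean time among relapsers, but no sentence says so. The absence of a censoring rule is not itself the fault. The fault is that the wording restricts the outcome, and the methods named would not bring the others back.

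Two smaller points also stand in part. The quit attempt in item vii is plausibly the one made at discharge from a smoke-free unit, so the origin is loosely worded more than plainly contradicted. The documents give no share of non-daily smokers and describe heavy nicotine dependence, so that gap may affect few people.

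None of this removes the mismatch between items iv and vii. A later analysis plan could add censoring, but it could not recover the start of a seven-day run if only the date of first smoking was asked.

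**Conclusion.** The point holds at moderate severity. Items iv and vii disagree on the event, the start of the clock needs stating, and on the plain wording the outcome is limited to a subgroup formed after randomisation. Such a comparison may dilute or distort the effect. At an assumed hazard ratio of 0.5 with constant hazard, a median ratio of 2.0 shrinks to about 1.2–1.4 and 58–73% of the restricted mean difference is lost. Under the delay pattern the loss is at most 15%.

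A reader might infer that non-relapsers carry most of the treatment effect and that the comparison is always pulled toward no effect. The documents do not support this, because both depend on the assumed pattern. The 9–33% range was also measured during treatment, and the Background says most relapsed after discharge. Fewer non-relapsers would mean less dilution.

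A reader might also infer that one puff on day 2 sets item vii against the primary outcome. It does not: without a seven-day run that person is no relapser, and item vii assigns no time. The mismatch affects those who lapse and relapse later.

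This is one of 13 secondary outcomes in an exploratory pilot. No primary result or sample-size figure rests on it, so power is not the yardstick here.

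**What to change.** Reconcile items iv and vii to one event, and start the clock at discharge for all randomised participants.

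- **Main definition.** Analyse time from discharge to first smoking, called time to first lapse. Censor those who have not smoked at their last completed contact. Report Kaplan–Meier curves and a log-rank test with a Cox hazard ratio and 95% confidence interval. In the 33% scenario above the END median (15.0 weeks) lies beyond follow-up, so do not rely on medians alone.
- **Data.** The date of first smoking is already asked. On the wording it is asked of those who relapse, so put it to everyone who reports any smoking.
- **If seven-day relapse is kept as a separate event.** Add the start date of the run to the 6- and 12-week surveys, and state how people who did not smoke daily before are classified.
- **Sensitivity.** Censoring at last contact assumes that loss is non-informative, which is hard to defend with 40% attrition expected. Add an analysis that counts those lost as relapsed.

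The cost is one rewritten outcome, one analysis sentence, a change in who is asked the date question and, optionally, one new date item. Recruitment began on 1 August 2017 (Trial status), so newly asked dates will be missing for participants already surveyed. That should be reported.

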
### Covariate measures

A number of covariate measures will be used for the statistical analysis, including:i.Demographic variables such as gender.ii.History of tobacco smoking and quitting.iii.Motivation to quit, assessed by a 10-point Likert scale where 1 is very low and 10 is very high [37].iv.Quitting self-efficacy, which is assessed using the following item: “If you decided to give up smoking completely in the next 6 months, how sure are you that you would succeed?” with response options: (1) not at all sure, (2) slightly sure, (3) moderately sure, (4) very sure and (5) extremely sure [38].v.Heaviness of smoking index: Nicotine dependence is assessed using the two-item Index [31, 32]. It uses a six-point scale calculated from the number of cigarettes smoked per day (1–10, 11–20, 21–30 or 31+) and the time to first cigarette after waking (≤5, 6–30, 31–60 or 61+ minutes). Nicotine dependence is then categorised into a three-category variable: low (0–1), medium (2–4) or high (5–6).vi.Alcohol Use Disorders Identification Test: Brief (AUDIT-C) [39, 40], which is a three-item screening tool used to identify hazardous alcohol use or active alcohol use disorders. It is scored on a scale of 0–12 with a cut-off of 3 (women) or 4 (men). For men, it has been shown to have a sensitivity of .90 and specificity of .45. For women, the sensitivity is .80 and specificity is .87 [39, 41].vii.Drug Use Disorders Identification Test (DUDIT) [42], an 11-item instrument designed to parallel AUDIT-C with a scale of 0–44. It has been shown to have a sensitivity of .90 and a specificity of .88, with a Cronbach’s alpha coefficient of .80 [42].viii.Kessler Psychological Distress Scale (Kessler-10) [43], a 10-item scale of non-specific psychological distress with low scores (10–15) indicating little or no psychological distress, moderate scores (16–21), high scores (22–29) and very high scores (30–50) indicating increasing levels of distress.

### Statistical methods

#### Sample size estimation

We expect to recruit 100 clients over a 10-month period. Approximately 80% of clients to the service are smokers. We will be assuming 50% eligibility and consent into the trial, and 40% attrition at 12 weeks based on our current AOD research. A total of 60 participants at the 12-week follow-up will provide 30 smokers per experimental group. This trial has been designed to provide essential preliminary information for the development of an adequately powered larger superiority trial, including smoking prevalence, response and attrition rates.

#### Statistical analysis plan

Data will be collected on recruitment and retention rates, which will aid the design of future larger trials. Primary cessation outcome analyses will be carried out on an intention-to-treat basis. We will use chi-squared tests to compute relative risks, 95% confidence intervals and two-sided *p* values for all binary variables, followed by adjusted multiple logistic regression analyses. Continuous outcomes (with 95% confidence intervals) will be analysed using generalised linear mixed methods regression for the main aims, with adjustments for covariates where necessary.

## Discussion

This randomised controlled trial will be the first to assess the effectiveness, feasibility and acceptability of ENDs within an AOD-dependent population in Australia. This study is targeting a high-priority group with a very high prevalence of smoking. In the short term, the project will provide essential information for the design of a larger superiority trial, which will be powered to assess the safety and efficacy of ENDs and/or NRT use for sustained cessation and harm reduction outcomes in AOD clients.

AOD-dependent people smoke at higher rates than the general population [1, 2] and suffer from a greater smoking-related disease burden [4, 5, 7]. This vulnerable population should be a target for harm reduction research as a public health priority. Further, clear-air laws mean that most residential treatment services are smoke-free. Patients in the services are required to abstain from combustible tobacco, and most services supply NRT in the form of patches for the duration of the stay. While many patients express a desire to quit, most report returning to smoking immediately after discharge from inpatient services [8]. Thus, the inpatient period is a unique window of opportunity for patients to experience forms of nicotine delivery other than combustible tobacco.

ENDs are a relatively new product with a rapid rise in use in the general population [44]. Research on the acceptability and feasibility of ENDs as an alternative to tobacco is relatively limited. However, the devices are considered to be a less harmful alternative to combustible tobacco [23], and have been found to improve cessation rates [26]. The particular devices used in the study were selected due to their relative affordability and reliability as well as ease of use, and they were not manufactured by a tobacco company. The strength of the e-liquid supplied is similar to a liquid nicotine product currently listed on the Australian Register of Therapeutic Goods, which is approved for over-the-counter sale in general retail outlets, Nicorette QuickMist Mouthspray. It contains 13.6 mg/mL of nicotine and each pack contains 13.2 mL (i.e. the total nicotine per pack is 179.5 mg). The 4-week supply of 8 × 10 ml bottles of liquid, a total supply of 80 ml, equates to approximately 3 ml of liquid per day, which is considered an appropriate amount of nicotine to be prescribed for such devices [45]. Recent studies suggest that devices such as those to be used in the current study have better nicotine delivery than existing NRT products [22, 46]. However, note that the specific END in the study is not currently approved by the Therapeutic Goods Administration for therapeutic use in Australia.

Another facet of the project is the referral to a quitline telephone counselling service. Telephone quitlines are low cost and convenient to access, they can be tailored to individuals, and they have the potential to reach a broad population of smokers. Australia has a national quitline service, with a common telephone number in each state and territory. The service provides evidence-based information and assistance in a single call (reactive) as well as repeated calls from trained counsellors (proactive). A Cochrane review found that quitlines are effective for the general population and that call-back counselling (proactive) enhances their usefulness (nine studies, >24,000 participants, relative risk 1.37 and 95% confidence interval 1.26–1.50) [47]. However, the utilisation of quitline services is low. For example, in Australia, it is estimated that only 3.2–3.6% of smokers access the service [48, 49]. Furthermore, there is no information about the engagement of the AOD population with quitlines. The proposed study will provide data on the engagement and acceptability of the quitline within this hard to reach group of smokers.

Possible challenges for the study include recruitment and retention rates. The AOD population is considered hard to reach and difficult to retain [50]. The reasons for the difficulty in retention are systemic, with disadvantages due to sociological and economic factors, as well as high comorbidity being an issue for the population. However, if the overall aim of health research is reducing health burden and increasing equity, it is those systemic issues that should drive research with this vulnerable population rather than deter it. Recruitment rates in this population may be low. In the proposed study, we aim to mitigate the issue by offering incentives in line with the project objectives (free NRT or ENDs), and including detailed information in the recruitment phase (benefits of quitting and requirements of participation). To control for attrition, we plan regular scheduled contact with participants over the course of the study, as well as gathering collateral contact details (up to four secondary contacts), and liaising with residential treatment services to maintain contact with participants who may go into long-term residential rehab during the study period.

The current study is not powered to detect small differences in cessation; however, it will provide valuable information on the feasibility, acceptability and potential effectiveness of ENDs as a smoking cessation and harm reduction aid with AOD populations, and inform the design of a larger, powered study. It will also provide safety and adverse events data. The project also lacks a no-intervention placebo, control group. However, the combination NRT group represents current best practice and this study was designed to test the feasibility of ENDs in this population compared with current best practice and to inform future larger-scale studies. Another limitation is that the study utilises self-reported cessation rather than any biomarker confirmation. Biochemical verification is recommended for studies using the Russell standard as an outcome measure [51]; however, experts have agreed that biochemical validation methods need not always be used to validate self-report smoking cessation measures [52]. While it is possible to include biochemical verification in a trial such as this, the limited funding available made it difficult to do so. Following consultation between all study investigators, it was decided that given the aims of the pilot trial were to test the acceptability and feasibility of ENDs, and the study is not powered to determine the effectiveness of smoking cessation (which would be the primary reason for biochemical verification), that the additional cost and resources (in staff time) required to complete the biochemical verification were not warranted. Note that the study authors have submitted a funding application for an adequately powered effectiveness randomised controlled trial, which will assess biochemically verified smoking cessation as the primary aim.

The trial will provide insights into the potential viability of providing smoking cessation interventions as clients leave a smoke-free residential setting. This is important because most resume smoking, typically as soon as they can access cigarettes [8]. In the longer term, this research will contribute to the evidence base to inform policy development regarding the adoption of smoking cessation and tobacco harm reduction approaches within the AOD treatment setting. Harm reduction is an approach commonly used within AOD treatment settings; however, it has not been applied empirically for tobacco smoking. The research will provide a model for how to incorporate cessation support in AOD settings, particularly residential smoke-free services, which present a unique opportunity for intervention and the adoption of harm reduction approaches.

